#### RESEARCH QUESTIONS

Does the use of game-based learning as an innovative self-directed learning strategy improve nursing undergraduates' self-directed learning abilities in comparison to conventional learning method?

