#### OBJECTIVES

1. To assess the effect of game-based learning as an innovative self-directed learning strategy on knowledge acquisition among nursing undergraduates.
2. To assess the effect of conventional learning method on knowledge acquisition among nursing undergraduates.
3. To evaluate the effect of game-based learning as an innovative self-directed learning strategy on self-directed learning abilities among nursing undergraduates.

4. To evaluate the effect of conventional learning method on self-directed learning abilities among nursing undergraduates.
5. To compare the impact of game-based learning and conventional learning method on knowledge acquisition among nursing undergraduates after 12 weeks of intervention.
6. To determine whether game-based learning is superior to conventional learning in improving self-directed learning abilities in nursing undergraduates after 12 weeks of intervention.

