##### INTERVENTIONS

Researcher will provide detailed information about purpose and procedures of the study to the participants. They will be ensured for the anonymity of participants' personal information and collected data. Participants will be made aware of approximate time needed to complete the questionnaire (around 15-25mins). They will be informed that there will be no penalty for not participating and they can withdraw at any time during the study. They will be assured that their responses would not have any effect on their academic ground and it will be kept confidential with researcher. A written informed consent will be taken from the subjects willing to participate in the study.

After signing an informed consent form, participants will undertake a pretest covering knowledge, self-directed learning abilities, and perceived learning competency. Following that, two batches of students on the basis of their academic semester will participate in a 90-minute structured teaching session on self-directed learning, where the students will be

engaged in group activity and the concept of self-directed learning, its importance and process will be discussed with them.

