**Self-directed learning module:**

| S. N | Activity                                                                                                                                                                                                                                                                                                                                                                        | Duration | T/L Method & Media                           |
|------|---------------------------------------------------------------------------------------------------------------------------------------------------------------------------------------------------------------------------------------------------------------------------------------------------------------------------------------------------------------------------------|----------|----------------------------------------------|
| 1    | Formulation of group                                                                                                                                                                                                                                                                                                                                                            | 15min    |                                              |
| 2    | 
 
• A common learning goal will be established
 
• Each group will be given a topic to carry out SDL to achieve common goal
 
• Each group will discuss the resources required for the topic, the methods of SDL they will be using to achieve the common goal
 
• Each group will present their SDL plan
 
  | 30min    | Chart paper for the presentation             |
| 3    | 
From the group activity- the concept of SDL, its importance, process will be discussed with the students.
 
 
• Establish learning goals
 
• Locate & access resources
 
• Adopt & execute learning activities
 
• Monitor & evaluate performance
 
• Reassess learning strategies
 
 | 45 min   | PPT and interactive discussion with examples |

Subsequently, the participants will be randomly assigned to either the intervention or control groups, using numbered envelop, by simple random sampling determined by a randomization list.

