**In Experimental group**

After a session on Self-directed learning, experimental group will be further divided into small teams and then exposed to AMS game. Researcher will act just as a facilitator and share gaming screen with the team and encourage group discussion.

Antimicrobial stewardship (AMS) game is developed by the Commonwealth Partnerships for Antimicrobial Stewardship Programme, (CwPAMS\*), led by Commonwealth Pharmacists Association (CPA) and Tropical Health Education Trust (THET) in partnership with Focus Games Ltd. AMS game is designed to teach the basics of Anti-microbial resistance, Anti-microbial stewardship and infection control, and also how they intertwine to impact global health. Players are challenged and entertained in this team game as they tackle various

scenarios, test their knowledge, and change behaviours that can ultimately save lives of people.

Immediate postintervention test following gaming session will be taken and schedule for next online AMS gaming session on first weekend along with zoom login ID and password will be shared to the experimental group participants. And login details for consecutive AMS gaming will be shared to them a day before weekend for two following weeks in their email. Altogether four gaming session will be conducted in a period of four weeks.

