#### In Control group

After Self-directed learning session, learning material on antimicrobial resistance, antimicrobial stewardship and infection control will be shared to all the participants and one hour will be given to them for self-study. Immediate post-test will be taken after one hour of self-study and encourage to do self-learning with provided learning material for four weeks.

---

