#### STRATEGIES TO IMPROVE ADHERENCE TO INTERVENTIONS

To improve adherence to intervention protocol, text message in WhatsApp and email will be send to all the participants. The researcher will interact with participants weekly for one month on a Zoom online platform to provide guidance on self-directed learning and answer questions about learning methods. However, no lectures will be given on the learning content so that outcome variables are not affected.

To promote participant retention and minimize the risk of communication between participants in the control and experimental groups during the 4-week of follow-up period, we will implement several strategies. Participants will be instructed on maintaining confidentiality of group assignments and intervention details. The control group will be assured of getting access to the AMS game at the end of the study to reduce tendency for seeking premature information. Only experimental group will get login code for zoom platform for playing AMS game, ensuring only the assigned group can attend each session. During the game-based learning session, all participants will be asked to keep their cameras on to ensure that only the experimental group participants are present.

---

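### Both arms get self-directed-learning training after the only SDLI pre-test, so pre-post change within an arm (Objectives 3 and 4) is not the effect of that arm's method, and the comparator needs one name

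*Protocol*

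**What the plan says.** The order of events is explicit in the Protocol.

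- Interventions: after consent, "participants will undertake a pretest covering knowledge, self-directed learning abilities, and perceived learning competency". This is the only SDLI measurement before treatment.
- Interventions, next: "two batches of students on the basis of their academic semester will participate in a 90-minute structured teaching session on self-directed learning". The batches are formed by semester, not by arm.
- Self-directed learning module, after the class: "Subsequently, the participants will be randomly assigned to either the intervention or control groups".
- In Experimental group: "After a session on Self-directed learning, experimental group will be further divided into small teams and then exposed to AMS game".
- In Control group: "After Self-directed learning session, learning material on antimicrobial resistance, antimicrobial stewardship and infection control will be shared to all the participants", followed by an hour of self-study and four weeks of encouraged self-learning. Under Posttrial care the experimental group gets this material only after week 12, so all participants here means all controls.
- Strategies to improve adherence to interventions: "The researcher will interact with participants weekly for one month on a Zoom online platform to provide guidance on self-directed learning". No arm is excluded.

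Objective 4 is "To evaluate the effect of conventional learning method on self-directed learning abilities among nursing undergraduates", and Objective 3 is its counterpart for the game. Statistical methods assigns pre-test to post-test differences to a paired t-test. The research question asks whether the game will "improve nursing undergraduates' self-directed learning abilities in comparison to conventional learning method".

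**The concern.** The class teaches students to set learning goals, find resources, carry out learning and monitor their own performance, and it does so through group planning and presentation. The SDLI scores motivation, planning and implementing, self-monitoring and interpersonal communication. The class is therefore aimed at the construct of the first primary outcome, and it falls between the SDLI pre-test and allocation. The weekly guidance continues the same training.

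Two things are at stake. First, any rise in SDLI within an arm mixes the arm's own method with training that everyone received. Objectives 3 and 4 nevertheless ask for the effect of each method taken singly. The Secondary Outcome section reasons in the same way for perceived learning, treating improvement in the experimental group as a sign that the intervention worked. Second, the comparator changes name from section to section, so a reader cannot tell what a result for or against H1 would mean.

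**Working it through.** **1. The plan's own figure.** Standardised effect 0.5, two-sided 0.05, power 80%: the exact t-test calculation gives 63.8, hence 64 per arm, with power 0.801 at 64. The Protocol's 64 is reproduced. Nothing in this point changes it.

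**2. Between arms.** Write the mean SDLI change as

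- game arm: class + guidance + game
- control arm: class + guidance + self-study

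The difference is game minus self-study; the shared terms cancel. Simulation check: 64 per arm, 4,000 runs, pre-post correlation 0.5, shared class effect 0.3 SD.

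| True game effect | Mean between-arm difference in change | Rejection rate, t-test on post-scores |
|---|---|---|
| 0 | 0.00 SD | 5.0% |
| 0.5 SD | 0.50 SD | 80.4% (80.0% with no class) |

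The test keeps its error rate and its power. If the training and the game do not act additively, the contrast is still valid. It is then the effect of the game among SDL-trained students, which is what the trial randomises.

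**3. Within one arm.** The Protocol gives no SDLI standard deviation, pre-post correlation or class effect, so all three are assumed, and the class gain is assumed to last until the post-test. With equal pre and post SDs, the SD of change is √(2(1 − r)) in SD units. For a class effect c and no effect of the arm's own method, the non-centrality of the paired t-test is c ÷ √(2(1 − r)) × √n. Example: c = 0.3, r = 0.5, n = 64 gives 0.3 ÷ 1 × 8 = 2.4, and a probability of 66%.

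Probability of a significant paired test when the arm's own method does nothing (nominal 5%):

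| Class effect | n = 64, r = 0.5 | n = 64, r = 0.7 |
|---|---|---|
| 0.1 SD | 12% | 17% |
| 0.2 SD | 35% | 53% |
| 0.3 SD | 66% | 86% |
| 0.5 SD | 98% | over 99% |

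With all 70 per arm and r = 0.6, the figures are 45%, 79% and 96% for class effects of 0.2, 0.3 and 0.4 SD.

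**4. The comparator, section by section.**

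| Section | Name used |
|---|---|
| Research questions; Hypothesis (H1); Objectives 2, 4 and 5 | conventional learning method |
| Objective 6 | conventional learning |
| Study design | conventional learning group |
| Aim | conventional self-directed learning strategy |
| Primary Outcome 2 | conventional SDL group |
| In Control group (what is delivered) | SDL class, learning material, self-study |

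The first three rows do not mention SDL. The last three do, and they match what both arms actually receive.

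**The case against.** The strongest reply is that the main result is safe. H1, Objective 6 and the definition of the SDLI outcome are all between-arm comparisons, and the class precedes allocation and goes to everyone. This stands. A reader might infer that the pre-class baseline biases the test of H1; step 2 shows that it does not. The pre-class SDLI also remains a valid pre-randomisation covariate.

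A second reply is that the control may well be conventional learning in the Protocol's sense. The term is never defined as learning without SDL training. The research gap table describes a pilot trial of self-regulated learning in which textbook use was the conventional method. This also stands. A reader might infer that the control is simply not the comparator H1 names, or that the title promises a comparison of SDL with no SDL. The documents support neither: Study design describes SDL using educational games against conventional learning. What can be shown is an undefined term used inconsistently.

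A third reply is that the sizes in step 3 are assumed. That is correct; they illustrate the problem and do not predict it. That change within an arm contains the shared training follows from the order of events alone.

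Finally, moving the SDLI pre-test to after the class is no clean cure. The weekly guidance would still be in the 4- and 12-week change. The same self-ratings would be repeated shortly before the immediate post-test, and scores might be briefly raised just after the class. This is why the move is only optional below.

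**Conclusion.** The point holds in a limited form. The randomised comparison is unbiased, but what it estimates is the added effect of the AMS game over self-study of learning material, with SDL training and guidance in both arms. It cannot show superiority over learning without SDL training, because no arm goes without it. The paired pre-post analyses for Objectives 3 and 4 cannot isolate the effect of either method. Under the assumptions in step 3, a class effect of 0.2 to 0.3 SD alone would make the control arm's test significant 35% to 86% of the time at 64 per arm. The comparator's name differs between the Aim and Primary Outcome 2 on one side and the research question, H1, Objectives and Study design on the other. This should be corrected because it changes what the trial may conclude. It gives no reason to change the sample size.

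**What to change.** 1. Use one comparator name in the research question, H1, Aim, Objectives, Study design and Outcomes, for example: self-study of learning material, on top of SDL training and guidance given to both arms.
2. State the estimated effect as the game's added effect over that comparator.
3. Report Objectives 3 and 4 as descriptive pre-post change, attribute no effect to either method from them, and rest conclusions on the between-arm comparison.
4. Draw no conclusion about superiority over learning without SDL training.

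These are wording changes. They need no extra participants, visits or instruments.

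Optional: repeat the SDLI after the class and before the envelopes are opened. This takes the class out of within-arm change but leaves the weekly guidance in. Its cost is one more questionnaire, given shortly before the immediate post-test. Item 3 is needed either way.

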**Self-directed learning module:**

| S. N | Activity                                                                                                                                                                                                                                                                                                                                                                        | Duration | T/L Method & Media                           |
|------|---------------------------------------------------------------------------------------------------------------------------------------------------------------------------------------------------------------------------------------------------------------------------------------------------------------------------------------------------------------------------------|----------|----------------------------------------------|
| 1    | Formulation of group                                                                                                                                                                                                                                                                                                                                                            | 15min    |                                              |
| 2    | 
 
• A common learning goal will be established
 
• Each group will be given a topic to carry out SDL to achieve common goal
 
• Each group will discuss the resources required for the topic, the methods of SDL they will be using to achieve the common goal
 
• Each group will present their SDL plan
 
  | 30min    | Chart paper for the presentation             |
| 3    | 
From the group activity- the concept of SDL, its importance, process will be discussed with the students.
 
 
• Establish learning goals
 
• Locate & access resources
 
• Adopt & execute learning activities
 
• Monitor & evaluate performance
 
• Reassess learning strategies
 
 | 45 min   | PPT and interactive discussion with examples |

Subsequently, the participants will be randomly assigned to either the intervention or control groups, using numbered envelop, by simple random sampling determined by a randomization list.

**In Experimental group**

After a session on Self-directed learning, experimental group will be further divided into small teams and then exposed to AMS game. Researcher will act just as a facilitator and share gaming screen with the team and encourage group discussion.

Antimicrobial stewardship (AMS) game is developed by the Commonwealth Partnerships for Antimicrobial Stewardship Programme, (CwPAMS\*), led by Commonwealth Pharmacists Association (CPA) and Tropical Health Education Trust (THET) in partnership with Focus Games Ltd. AMS game is designed to teach the basics of Anti-microbial resistance, Anti-microbial stewardship and infection control, and also how they intertwine to impact global health. Players are challenged and entertained in this team game as they tackle various

scenarios, test their knowledge, and change behaviours that can ultimately save lives of people.

Immediate postintervention test following gaming session will be taken and schedule for next online AMS gaming session on first weekend along with zoom login ID and password will be shared to the experimental group participants. And login details for consecutive AMS gaming will be shared to them a day before weekend for two following weeks in their email. Altogether four gaming session will be conducted in a period of four weeks.

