#### **SAMPLE SIZE**

The study hypothesize that the self-directed learning abilities and knowledge acquisition among participants attending the game based learning would be superior to those attending the conventional learning. The sample size is determined using G\*Power (Version 3.1.9.7). Assuming a significance level of 0.05 and effect size of 0.5 (based on meta-analysis study\* which estimated a medium effect size in favor of game-based learning over learning without gamification), 64 participants per arm will be required to achieve a statistical power of 80%. Considering a dropout rate of 10%, 70 participants per arm, 140 participants in total, is required.

- Census sampling will be done to eliminate the selection bias. All the basic Bsc.Nursing students from two semester will be enrolled in study with hundred in each experimental and control group. Total 200 students is planned to be enrolled.

---

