## STATISTICAL METHODS

The study will use SPSS version 21, with tests like Shapiro-wilk, skewness, and kurtosis to evaluate the normal distribution of variables. Pre-test homogeneity will be assessed using descriptive statistics, independent t-tests, chi-square tests, and Fisher's exact test. ANOVA will compare differences in SDL ability, PL competency, and knowledge between groups. Regression analysis will explore the relationship between independent variables and dependent outcomes. Differences between pre-test and post-test will be analyzed using paired t-test. All statistical analysis will be two-sided, with a p-value less than 0.05 considered statistically significant.

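### Only game-arm students are taught in teams, yet the sample size and ANOVA treat all students as independent; if team-mates' scores correlate, type I error exceeds 5% and power at 64 per arm is overstated

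*Protocol*

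**What the plan says.** Under Allocation, individual students are randomised 1:1. Under In Experimental group, after allocation, the "experimental group will be further divided into small teams and then exposed to AMS game", and the researcher is to "share gaming screen with the team and encourage group discussion". Four game sessions run over four weeks. The section does not give the size or number of teams, or say whether they stay the same from session to session. Under In Control group, students receive learning material and an hour of self-study; no teams are mentioned.

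Under Sample size: "Assuming a significance level of 0.05 and effect size of 0.5", from which "64 participants per arm will be required to achieve a statistical power of 80" per cent. Then: "Considering a dropout rate of 10%, 70 participants per arm, 140 participants in total, is required". The same section also states a different plan: "Total 200 students is planned to be enrolled", that is, 100 per arm.

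Under Statistical methods: "ANOVA will compare differences in SDL ability, PL competency, and knowledge between groups". Also: "All statistical analysis will be two-sided, with a p-value less than 0.05 considered statistically significant". Neither section mentions teams, an ICC or a design effect. The inventory under Data collection methods has no field for team membership.

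**The concern.** This is a partially nested design: individual randomisation, with grouping created by the intervention in one arm only. Team-mates watch the same play and hear the same explanations and errors. Their scores may therefore resemble each other more than those of students from different teams. The outcomes most exposed are the two primary ones: a knowledge test on the content that was discussed, and the SDLI, one of whose four domains is interpersonal communication.

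With positive correlation within teams, the mean of the game arm varies more than the ANOVA assumes. Intervals are then too narrow and p-values too small, and the error favours a false claim of a difference in a trial declared as a superiority study. An analysis that allows for teams has less power than the sample size section states.

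**Working it through.** **Inputs from the protocol.** d = 0.5 (so SD = 1), two-sided alpha 0.05, n = 64 evaluable per arm, or 100 per arm under the alternative plan.

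**Assumed inputs (not in the protocol).** Team size m = 4 to 8, ICC = 0.02 to 0.10, one ICC for the time point analysed, each control independent.

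**1. Reproduce the stated figure.** For an independent two-sample t-test with 64 per arm, the noncentrality is 0.5 × √(64/2) = 2.828 on 126 df. Power is 80.1%. The 64 is therefore a calculation for independent observations with no allowance for teams.

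**2. Variance with teams in one arm.** Design effect DE = 1 + (m − 1) × ICC, applied to the game arm only. SE = √(DE/n + 1/n).

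**3. Type I error of the unadjusted test.** It uses SE₀ = √(2/n), so the true level is 2 × [1 − Φ(1.96 × SE₀/SE)] = 2 × [1 − Φ(1.96 × √(2/(DE + 1)))]. The n cancels, so a larger trial does not reduce the inflation.

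**4. Power of a team-adjusted test.** Noncentral t with noncentrality 0.5/SE and Satterthwaite df, where the game arm contributes (number of teams − 1) and the control arm n − 1.

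**5. One cell in full (m = 6, ICC 0.05, n = 64).** DE = 1 + 5 × 0.05 = 1.25. SE = √(1.25/64 + 1/64) = 0.1875, against SE₀ = 0.1768. Type I error: 1.96 × 0.1768/0.1875 = 1.848, giving 6.5%. Power: noncentrality 0.5/0.1875 = 2.667, 64/6 = 10.7 teams, df = 28.5, critical t = 2.047, giving 73.1%.

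**6. The range at 64 per arm.**

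| m | ICC | DE | Type I error, unadjusted | Power, team-adjusted |
|---|---|---|---|---|
| 4 | 0.02 | 1.06 | 5.3% | 77.9% |
| 4 | 0.05 | 1.15 | 5.9% | 76.1% |
| 4 | 0.10 | 1.30 | 6.8% | 73.1% |
| 6 | 0.05 | 1.25 | 6.5% | 73.1% |
| 8 | 0.02 | 1.14 | 5.8% | 74.5% |
| 8 | 0.05 | 1.35 | 7.1% | 69.9% |
| 8 | 0.10 | 1.70 | 9.2% | 63.1% |

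Simulation of the unadjusted t-test (20,000 or more runs per cell) gave 5.2% to 5.4% in the lowest cell and 9.1% to 9.4% in the highest.

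**7. How much is clustering and how much is few teams.** With the same formula and ICC 0, power is 79.2% for m = 4 and 77.6% for m = 8, because the df rest on 16 or 8 teams. So up to 80.1 − 77.6 = 2.5 points of the loss come from the small number of teams. A normal approximation that ignores the df gives 74.2% for m = 8, ICC 0.05 and 68.2% for m = 8, ICC 0.10, against its own baseline of 80.7%.

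**8. The 200-student plan.** With 100 evaluable per arm, power is 92.0% (m = 4, ICC 0.05), 88.6% (m = 8, ICC 0.05) and 83.6% (m = 8, ICC 0.10). After 10% dropout (90 per arm) the last two become 84.9% and 79.2%. By step 3, type I error is unchanged.

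**The case against.** The strongest reply is that nothing in the protocol shows the correlation to be more than trivial. There is no ICC and no team size. At ICC 0.01 with teams of 4, type I error is about 5.2%. Teams are described at the first exposure only; later sessions are online, and if teams are reshuffled the correlation would be diluted. Objectives 5 and 6 place the comparison at 12 weeks, when a team effect may have faded. All of this stands, which is why the size is conditional.

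The power argument also depends on which enrolment plan is followed. At 100 evaluable per arm it largely disappears. That stands too, but the type I error does not improve with n.

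Treating each control as independent is also an assumption: the protocol does not say where the self-study hour takes place, and weekly online guidance is offered to participants generally. Omitting semester, the stratification factor, from the ANOVA would push p-values slightly the other way. The protocol gives no figure for either effect.

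Finally, an SAP that is not shown may name a mixed model. However, the protocol itself fixes an ANOVA and a sample size that assume independence. Team membership that is not recorded during the sessions may not be recoverable at analysis.

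**Conclusion.** The point holds in conditional form. The mismatch between team delivery in one arm and an independent-students calculation and analysis is plain from the text, and the direction is certain for any positive ICC. The size is not known. Over the assumed range (teams of 4 to 8, ICC 0.02 to 0.10, 64 evaluable per arm) the unadjusted test has about 5.2% to 9% type I error and a valid test about 78% to 63% power. The middle of the range, 6 per team and ICC 0.05, gives about 6.5% and 73%.

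Three stronger readings are not supported. A reader might infer that the p-values will certainly be too small; the protocol does not establish that scores correlate. A reader might infer that the trial as a whole is underpowered; that applies to 64 per arm, and the protocol also plans 200 students, where power stays at about 84% or more over this range with 100 evaluable per arm. A reader might expect baseline adjustment to recover the lost power; the protocol gives no pre/post correlation from which to judge that.

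**What to change.** - State the intended team size and whether teams stay the same. Record a team ID for each game-arm student at every game session. How teams are formed need not change.
- For the between-group comparison, replace the plain ANOVA with a partially nested mixed model: a random team effect in the game arm only, each control as its own unit, and small-sample degrees of freedom. If teams change between sessions, say in advance which session's team enters the model at each time point.
- Decide between the 140 and 200 enrolment figures. Restate power for that size with an assumed team size and a range of ICC values.

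The cost is one extra variable, which must be in place before the first session, and one extra model term. The interval will be somewhat wider and the stated power less favourable.
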